#### Secondary outcome measures

The secondary outcome measures are the number of unplanned or unscheduled health care emergency department visits, quality of life, self-efficacy, time management, health-related distress, and feasibility and acceptability of a modified self-management program designed for adolescents with a chronic condition which include:

- Hospital admissions and emergency department visits due to chronic illness will be obtained from the medical records or My Health Record system if the young person is registered. An unplanned hospital admission is defined as an admission that is not part of routine illness management, not from an admission waiting list and which can be associated with a deterioration of illness control as a result of insufficient self-management practices [51]. These measures will be collected in all study participants at baseline in both standard care and intervention groups as with other measures except the feasibility and acceptability questionnaire at interval periods of 3, 6, and 12 months from baseline. The median and range of numbers of unplanned hospital admissions per person in each group will be described.

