### Objectives and hypothesis {7}

#### Primary research question

Does a modified adult chronic condition self-management program plus standard care improve therapy adherence in adolescents aged 15–18 years with a chronic condition compared to standard care only?

The *primary objective of this stud*y is to investigate the effectiveness via adherence of a modified adult chronic condition self-management support program in an adolescent population with a chronic condition within a tertiary pediatric hospital setting, compared to those receiving routine care services in the same setting using standardized markers of improvement in control of their chronic illness.

The *secondary objectives* include the use of routinely collected data on the number of unplanned or unscheduled health care or emergency department visits, together with questionnaire measures of quality of life, self-efficacy, time management, health-related distress, and feasibility and acceptability of the program to further refine its delivery under clinical conditions.

*Study hypothesis* to be tested is that a modified adult-focused, generic chronic condition self-management support program provided to adolescents with a chronic condition who are in the active phase of transition to adult services would:Be more effective than standard usual care in achieving adherence to chronic condition management as measured by quantitative condition-specific validated markers of improvement in illness control as described in Table 1.Be more effective than standard care in improving more global quality of life, self-efficacy, time management, and in reducing health-related distress as described in Table 2.

**Table 1 Tab1:** Markers of illness control

Chronic condition	Measures of illness control	Definition of improvement^*^
Cystic fibrosis	▪ FEV1	FEV1% of predicted increased by ≥ 10%
Type 1 diabetes mellitus	▪ HbA1c	Absolute decrease in HbA1C by ≥ 1% (e.g., 9% reducing to 8%)
Inflammatory bowel disease	▪ Weight	Absolute increase in weight by ≥ 5%
Chronic kidney disease	▪ GFR	Absolute increase in GFR by ≥ 5%
Asthma	▪ FEV1	FEV1 % of predicted increased by ≥ 10%
Epilepsy	▪ Number of seizures	Based on individual and type of seizure as negotiated with treating Neurologist.

Abbreviations measures of illness control: *FEV1 (%)* forced expiratory volume in 1 s, *HbA1c* glycosylated hemoglobin (mmol/mol), *GFR* glomerular filtration rate (mL/min)

Weight (kilograms)

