Following randomization, participants in the intervention group will receive a 12-month nurse-led modified version of the Flinders Program™ plus standard care, while participants in the waitlist control group will receive standard care for 6 months before crossing over to the intervention group until all participants are exposed to the program as demonstrated in the study design diagram in Fig. 1. Participants in the intervention group will receive the Flinders Program™ which will be delivered individually, using a combination of face-to-face and telehealth sessions by members of the research team who have been trained in the delivery of the Flinders Program™. The initial face-to-face session will be undertaken in a private room within a clinic environment. Subsequent follow-up sessions will be offered via telehealth modality, either a video conferencing platform or telephone depending on the young person’s preference. Between the delivery of the initial session and 3 months follow-up, participants will receive follow-up consisting of a maximum of 3 phone calls (every 3 weeks), on a date a time agreed between the nurse and the patient. Participants will receive a booster session at 6 months to maintain engagement, monitor progress, and provide feedback and motivation to help them achieve their self-management goals. There is a final follow-up session at 12 months. Figure 1 outlines this process.

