#### Follow-up data collection

Adherence to prescribed treatment regimenBaseline observations will be collected from both the waitlist control group and the intervention group before randomization. Potential participants in the intervention group will be contacted via phone by a member of the research team. Follow-up of participants in the intervention group will be undertaken by a member of the research team via phone or telehealth (depending on the young person’s preference) at 3, 6, and 12 months to follow-up on adherence to the prescribed treatment post intervention. Participants who do not respond to 3 attempts to contact them at any time point will be treated as missing data.

Information from the participants will be obtained by completing the PIH scale via a semi-structured interview. Subsequently, participants allocated to the wait list control group will be contacted by phone by a member of the research team and provided with a self-management information brochure, with no further contact from the research team. At 6 months, participants in the waitlist control group will be contacted by phone by a member of the research team and invited to participate in the intervention as described for the initial intervention group.(b)Markers of illness control and unplanned hospital visits

The research team will obtain standard measures of illness control for all participants who have been recruited into the study and who have consented to clinical information being obtained for research purposes. The control of chronic illness is the best quantitative measure of therapy adherence that is available. This will be undertaken by way of the research team extracting information from the electronic medical records (EMR) and the young person’s primary physician contacted for further information. Data on unplanned hospital visits will be retrieved by the research team from EMR and/or accessed through the young person’s My Health Record if available.

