### Provisions for post-trial care {30}

Post care trial provisions have been outlined in the young person information sheet. In the event of health care needs arising as a direct consequence of trial participation in relation to emotional distress or psychological upset or discomfort, the participant’s primary treatment team and their parents/carers will be notified. Participants are also advised that they may leave the study at any time. Participants ineligible for inclusion in the current study will be offered the self-management clinic as a standard care option if and when required.

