## Assignment of interventions: blinding

### Who will be blinded {17a}

This trial is not blinded. As with all studies of this type of intervention, it is not possible to blind trial participants or the researchers who must know what group the participant is assigned to. To avoid potential bias during the statistical analysis of the trial, the data analyst will be blinded until the entire analysis has been completed.

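### Unplanned admissions are counted through a causal judgement about self-management, with no blinded classification stated, so the count can differ by arm for reasons other than admissions

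*Protocol article*

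**What the plan says.** The objectives section sets a broad secondary target: "the number of unplanned or unscheduled health care or emergency department visits". The Secondary outcome measures section then narrows it in two ways.

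- For all hospital contacts there is a restriction by cause: "Hospital admissions and emergency department visits due to chronic illness will be obtained from the medical records".
- For admissions there is a definition. It opens with administrative tests: "An unplanned hospital admission is defined as an admission that is not part of routine illness management, not from an admission waiting list". It then adds, joined by the word *and*, a further condition: "which can be associated with a deterioration of illness control as a result of insufficient self-management practices".

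Three other places bear on who makes the classification.

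- Follow-up data collection: "Data on unplanned hospital visits will be retrieved by the research team from EMR", or from My Health Record where available.
- Intervention description {11a}: the program is delivered "by members of the research team who have been trained in the delivery of the Flinders Program".
- Who will be blinded {17a}: "it is not possible to blind trial participants or the researchers who must know what group the participant is assigned to". Only the data analyst is blinded.

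The Secondary outcome measures section promises a median and range of admissions per person in each group. Statistical methods {20a} adds between-group tests, with Poisson regression for counts. The Partners in Health (PIH) scale section also names unscheduled admission, alongside illness control, when it restates the primary outcome.

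**The concern.** Whether an admission was scheduled or came from a waiting list can be read from the record. Whether it followed from insufficient self-management is an opinion about cause, and the opinion concerns what the program treats. Someone who knows that a participant has had coaching and holds a care plan may be slower to blame an admission on poor self-management. They may equally be quicker, because the coaching sessions have recorded every lapse.

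The information behind the judgement also differs by arm. Intervention participants have an interview, a care plan, telephone calls and reviews. Until month 6, waitlist participants receive a brochure and, apart from a call about the start date, no contact with the research team. Even a careful assessor would be judging the two arms on unequal evidence.

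At stake is the between-arm comparison of unplanned admissions. A difference could arise from classification alone, and blinding the analyst cannot remove a difference that is already in the data.

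**Working it through.** **The protocol's own figures.** No admission rate, classification rate or power statement is given for this outcome. The only power figure (27 per group, 15% versus 50%, 80% power, two-sided 5%, chi-square) reproduces at 27 per group with 80.2% power. It concerns the illness-control response and does not bear on this point.

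**The chain in the text.**

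1. The self-management condition is joined to the administrative tests by *and*, so failing it removes the admission from the count.
2. The research team retrieves the records.
3. Members of that team deliver the program.
4. The researchers know the allocation.
5. No rule for applying the condition and no blinded assessor is stated.
6. The analyst is blinded but works on events already classified.

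Steps 1 to 4 and 6 are stated in the text. Step 5 is an absence. That the unblinded team applies the condition is an inference from steps 2 to 5.

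**What unequal classification would do.** Let both arms have the same true rate λ per person, with n = 30 per arm (the recruitment target of 60 split 1:1). Let q_C and q_I be the shares of control and intervention admissions judged to qualify. The expected counts are nλq_C and nλq_I, so

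apparent rate ratio = nλq_I / nλq_C = q_I / q_C.

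All values of λ, q_C and q_I below are assumptions. With q_C = 0.90:

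- q_I = 0.80: 0.80/0.90 = 0.89
- q_I = 0.70: 0.70/0.90 = 0.78
- q_I = 0.60: 0.60/0.90 = 0.67

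If the inequality ran the other way (q_C = 0.70, q_I = 0.90), the ratio would be 0.90/0.70 = 1.29, against the program.

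False-positive rates were simulated with Poisson counts, 200,000 repetitions per cell, and a two-sided 5% Wald test on the log rate ratio:

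| Admissions per person (λ) | 90% vs 90% | 80% vs 90% | 70% vs 90% | 60% vs 90% |
|---|---|---|---|---|
| 0.5 | 4% | 5% | 8% | 14% |
| 1 | 5% | 7% | 13% | 26% |
| 2 | 5% | 9% | 23% | 47% |

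Columns give the intervention share, then the control share. With equal classification the error rate stays at its nominal level, whatever share is dropped. The harm comes from inequality between arms.

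**Scale in a small trial.** Assume 20 true admissions per arm, with 18 kept in control and 14 in intervention. The ratio is 14/18 = 0.78, and the standard error of its log is √(1/14 + 1/18) = 0.356. The 95% interval is 0.39 to 1.56, p about 0.48. With 19 and 17 kept, the ratio is 17/19 = 0.89, p about 0.74. At such counts the bias shifts the estimate more than it produces significant results.

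**The case against.** Several counter-arguments have force.

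- **The test is loose.** The text asks only whether an association can be made. All participants enter with unsatisfactory control and a need for self-management skills, so most illness-related admissions might pass in either arm. This limits the likely inequality. It does not remove it, and a loose test leaves more to the assessor.
- **Who applies the clause is not stated.** This is correct. The source cited for the definition and the fuller analysis plan are not shown, and either may hold an operating rule. Still, the protocol fixes the counting condition itself, and that condition is the problem.
- **A cause-specific outcome suits an adherence objective.** This is fair, and it is why an illness-related subset should stay. It does not require the main count to depend on a judgement about self-management.
- **The magnitudes are assumed.** They are, including the direction.

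A reader might also infer more than the text supports.

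- *That the count cannot show harm.* If the program worsened self-management or control, the resulting admissions would qualify. Only other causes drop out.
- *That this is the trial's main harm signal.* No section gives it that role. Adverse event reporting and harms {22} sends events possibly attributable to the intervention to the ethics committee, and distress is measured with the K10. Provisions for post-trial care {30} separately provides for needs arising "as a direct consequence of trial participation in relation to emotional distress or psychological upset or discomfort".
- *That emergency visits face the same self-management test.* They do not. They need only be due to the chronic illness.
- *That medication-related or distress-related events can never be counted.* An emergency visit for an adverse effect of chronic-illness treatment could be read as due to that illness.

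**Conclusion.** The point holds in a limited form. The definition makes a causal judgement on the program's own target a condition for counting an admission. No blinded classification is stated, and the team that handles the records knows the allocation. The comparison of unplanned admissions is therefore open to bias that the analysis cannot undo. Size and direction cannot be derived from the documents, and the ratios of 0.67 to 0.89 only show what assumed inequalities of 10 to 30 percentage points would produce. It would be wrong to conclude that the count necessarily favours the program.

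Admissions from other causes are absent from this count, though not necessarily from all reporting. The adverse event route may pick them up, but what goes to the ethics committee again depends on the research team's view of attribution. The outcome is listed as secondary. The point would matter more if the sentence in the PIH section that places unscheduled admission within the primary outcome were taken at its word.

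**What to change.** In Secondary outcome measures:

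1. Count unplanned admissions by the two administrative tests alone, whatever the cause, and drop the self-management clause from the counting rule.
2. Report illness-related admissions and emergency visits as a subset, classed from the coded discharge diagnosis or by someone blind to allocation.
3. Tabulate all-cause admissions and emergency visits by arm.

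The same records are already being searched, so the cost is mainly wording. If discharge codes are not usable, a blinded assessor is a modest extra task for 60 participants. The downside is noise from unrelated admissions, such as injuries, in the all-cause count; the illness-related subset largely answers that.

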#### Partners in Health (PIH) scale

The primary outcome is to determine the effectiveness of using a modified version of the Flinders Program™ as measured by illness control and unscheduled hospital admission as described above. Improvements in self-management will be measured using the validated PIH scale which is incorporated in the Flinders Program™ and provides a formal, low burden scale (usually takes less than 10 min to complete) designed specifically to measure improvements in self-management behaviors and health outcomes over time [46].

The PIH scale assesses self-management capacity using a validated Likert self-rated scale (0 being very little to 8 a lot) for each of the 12 questions covering the principles of self-management including knowledge and treatment of the condition (Q1 and 2); engagement with health care providers (Q3 and 4); access to services (Q5 and 6), monitoring and responding to signs and symptoms (Q7 and 8); physical, social, and emotional impacts of living with a chronic illness (Q9, 10, and 11) and lifestyle risk factors (Q12) [52, 53]. Questionnaires will be completed by all participants independently at commencement of the study as detailed in the study timeline. Scores of less than or equal to 4 are flagged by the health professionals as areas to be addressed. The PIH Scale demonstrates high internal consistency (0.81) and construct validity with a 4-factor analysis for knowledge, symptom management, adherence, and coping accounting for 80% of the variance [54]. The number and percentage of each randomized group who have a score of less than or equal to 4 will be collected at each timepoint 3, 6, and 12 months from baseline.

#### Health-related quality of life

Health-related quality of life will be measured using the Paediatric Quality of Life Inventory (PedsQL) version 4.0, an instrument that measures health-related quality of life (HRQOL) in children and adolescents from the age of 2–18 years. The PedsQL 4.0 Generic Core Scale is designed to incorporate four scales; physical (8 items), emotional (5 items), social (5 items), and school functioning (5 items) as delineated by the World Health Organization [55]. It comprises an adolescent self-report and assesses generic and disease-specific quality of life. For this study, the validated teenage report for ages 13–18 years will be used. This report was chosen as it is brief and easily administered and does not necessitate a large burden on respondents. The teenage report consists of 23 items which participants rate on a 5-point Likert scale with higher scores indicating better quality of life [56, 57]. The psychometric evaluations of the PedsQL 4.0 demonstrated high internal consistency (0.88). Validity was demonstrated using the known-group method, correlations with indicators of morbidity and illness burden [58]. This HRQOL measure was chosen as it is well validated in pediatric patients with acute and chronic conditions and takes into consideration the cognitive developmental needs of young people [55].

#### Time Management Questionnaire (TMQ)

Time management skills have demonstrated a level of effectiveness in both academic and non-academic contexts demonstrated through increased awareness of study habits, reduction in stress, self-regulation of time, and increased levels of self-efficacy [59]. An adaptation of the Time Management Questionnaire (TMQ) developed by Britton & Tesser [60] will be used in this study to assess attitudes and planning of participants. The questionnaire consists of 18 items using a 5-point response scale used consisting of never (1); rarely (2); sometimes (3); often (4); and always (5) with higher scores (except items 2, 3, 9, and 15) correlating to better time management. The TMQ incorporates 3 subscales including short-range planning, time attitudes, and long-range planning. This theoretical model was chosen as it has been validated for use in high school students aged 16–18 years and best suited to our population group [59] and was shown to have a reasonable level of internal consistency across the 3 subscales and total overall scale (0.87) [61]. It is unlikely that participants in our study will not be enrolled in any form of education. In the event that this is the case, we will ask them to omit questions which are specifically related to school.

#### Kessler Psychological Distress Scale (K10)

The Kessler Psychological Distress Scale (K10) is a well-recognized instrument which has demonstrated content and construct validity for measuring non-specific symptoms of psychological distress including behavioral, emotional, cognitive, and psychophysiological manifestations [62]. Initially developed for the US National Health Interview Survey (NHIS), the 10-item scale (K10) has been extensively used in both clinical and general populations including adolescents, and used in a variety of cultural and sociodemographic backgrounds [63]. The K10 scale measures the frequency of symptoms (nervousness, hopelessness, sadness, worthlessness, and fatigue) experienced in the past month using a 5-point Likert scale ranging from none of the time (1) to all of the time (5), producing a total score range of 10–50 with higher scores correlating to more distress [62]. A study conducted by Sampasa-Kanyinga et al. found that the K10 scale has satisfactory psychometric properties for use as a measure of non-specific psychological distress with high internal consistency (0.84) [64].

Adolescents with a chronic condition are more likely to develop psychiatric and behavioral disorders including depression and low self-esteem than their healthy counterparts. Thus, the K10 scale was chosen as it presents as a useful tool in identifying psychological symptoms in participants, and from our previous clinical experience in working with adolescent populations, the accessibility and simplicity of the K10 scale makes it an ideal instrument to use within this population group. [65]. It is not a diagnostic tool.

The mean and standard deviation of the scores for the outcome measures described above will be described in each group and at each time point, following randomization at baseline, 3 months, and 12 months.

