^*^Sustained improvement in measure of disease control over a 12-month period from baseline

**Table 2 Tab2:** Schedule of enrolments, interventions, and assessments

Procedure												
**Measure**	**Baseline**		**3 months**		**6 months**		**9 months**		**12 months**		**18 months**	
	**I**	**C**	**I**	**C**	**I**	**C**	**I**	**C**	**I**	**C**	**I**	**C**
Informed consent	**X**	**X**										
Demographic data collection	**X**	**X**										
Measures of illness control	**X**	**X**	**X**		**X**	**X**		**X**	**X**	**X**		**X**
Unplanned hospital visits	**X**	**X**	**X**		**X**	**X**		**X**	**X**	**X**		**X**
Questionnaires	**X**	**X**	**X**			**X**		**X**	**X**			**X**
Partners in Health (PIH) Scale	**X**	**X**	**X**		**X**	**X**		**X**	**X**	**X**		**X**
Feasibility and Acceptability Questionnaire (FAQ)									**X**			**X**
Flinders Program delivery	**X**		**X**		**X**	**X**	**X**	**X**	**X**	**X**		**X**
Booster session					**X**					**X**		

***I*** Intervention (Flinders Program plus usual care), ***C*** Control (waitlist plus usual care)

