## Data collection and management

### Plans for assessment and collection of outcomes {18a}

Patient demographic data will be collected at baseline (see Additional file 3). All data collection questionnaires are programmed in Research Electronic Data Capture (REDCap) and include Partners in Health (PIH) Scale, collected at baseline, 3, 6, and 12 months follow-up. Paediatric Quality of Life Inventory (PedsQL) version 4.0 (Teenage Report); Time Management Questionnaire; Kessler Psychological Distress Scale (K10) collected at baseline, 3 months, and 12 months follow-up. Additional data on makers of illness control and unplanned hospital admissions and emergency department visits will be obtained from the EMR at baseline, 3, 6, and 12 months follow-up. Data questionnaire on feasibility and acceptability will be collected on completion of the study at 12 months (see Additional file 4). Data will be collected and stored in REDCap a secure web-based application used for designing and managing clinical research databases. REDCap is an online data capture tool which stores data in a secure and encrypted manner on the University of Sydney server to which we have access [68]. This research data management platform is a secure web-based software platform used for the data management procedures of this trial including data collection, follow-up, and analyses. The built-in component of REDCap has been pre-prepared to accept only variables within given permissible ranges that are consistent with previous entries before going on to the next section to minimize missing values. Data collection forms pertaining to the study will also be stored in REDCap.

Prior to the commencement of the study, research staff completed the Flinders training workshop conducted over 2 days, by the lead research nurse (JG) who is an Accredited Flinders Trainer. All research staff were assessed as competent against current Flinders competency standards. The training was guided by validated manuals (Accredited Trainer: Flinders Chronic Condition Management Program Manual; The Flinders Chronic Condition Program Participant Manual) with electronic copies of all training resources and PowerPoint presentations available to ensure reproducibility and fidelity of the intervention program.

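### If Table 2 is followed, the two arms share no post-baseline visit for PedsQL, TMQ and K10, and the conflicting text does not restore a comparison with usual care

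*Protocol article*

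**What the plan says.** Objectives and hypothesis {7} lists, among the secondary objectives, "questionnaire measures of quality of life, self-efficacy, time management, health-related distress". The second hypothesis is superiority over standard care on these, with Table 2 cited for the measures. Statistical methods {20a} plans tests between randomized groups for the other study outcomes, and models for repeated observations where outcomes are longitudinal.

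The protocol gives three accounts of when the questionnaires are collected.

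- **Table 2**, titled "Schedule of enrolments, interventions, and assessments", marks the Questionnaires row for intervention at baseline, 3 and 12 months and for control at baseline, 6, 9 and 18 months.
- **The K10 subsection and section {18a}** give baseline, 3 and 12 months. The first covers the scores described before it and says they "will be described in each group and at each time point, following randomization at baseline, 3 months, and 12 months". The second has "Kessler Psychological Distress Scale (K10) collected at baseline, 3 months, and 12 months follow-up", with PedsQL and TMQ in the same sentence and no distinction by arm.
- **Secondary outcome measures** says that measures other than the feasibility questionnaire are collected in both groups "at interval periods of 3, 6, and 12 months from baseline".

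On contact with controls, Follow-up data collection says they are "provided with a self-management information brochure, with no further contact from the research team". The next contact described there is the 6-month invitation to start the program. Standard care procedures adds one call, a month before the start, solely to give the start date. Trial design {8} has controls cross over to the program at 6 months.

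**The concern.** A comparison with usual care needs both arms measured at the same time while controls are still unexposed, that is, up to the 6-month crossover. In Table 2 the intervention arm's only questionnaire in that window is at 3 months and the control arm's only one is at 6 months. Each arm is measured when the other is not.

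At stake is the randomized evidence for the quality-of-life, time-management and distress parts of the second hypothesis. These are self-report scores. Unlike laboratory markers or admissions, they cannot be recovered from the record if they were not collected on time. A later analysis plan can choose a model, but it cannot supply missing measurements.

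**Working it through.** There is no plan figure to reproduce. Sample size {14} covers only the primary response rate, and its 27 per group (15% against 15% + 35% = 50%, 80% power) reproduces but does not bear on this point. The check is a cell-by-cell reading of Table 2, whose rows each have 12 cells (6 visits × 2 arms).

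| Table 2 row | Intervention (months) | Control (months) | Shared after baseline |
|---|---|---|---|
| Questionnaires | 0, 3, 12 | 0, 6, 9, 18 | none |
| PIH scale | 0, 3, 6, 12 | 0, 6, 9, 12, 18 | 6, 12 |
| Illness control | 0, 3, 6, 12 | 0, 6, 9, 12, 18 | 6, 12 |
| Unplanned visits | 0, 3, 6, 12 | 0, 6, 9, 12, 18 | 6, 12 |
| Program delivery | 0, 3, 6, 9, 12 | 6, 9, 12, 18 | not an outcome |

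**Is the table misread?** The Questionnaires row has 3 + 4 = 7 marks and the PIH row 4 + 5 = 9, with no cell lost. The control pattern also makes sense in program time: with a start at 6 months, visits at 9 and 18 are 9 − 6 = 3 and 18 − 6 = 12 months into the program. So the row does not look shifted or broken. It repeats the intervention arm's 0, 3 and 12 in the control arm's own program time.

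**Which contrasts remain under Table 2?**

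- Same calendar time: none after baseline.
- Same program time (intervention 3 and 12 against control 9 and 18): both arms are then treated, so this says nothing about standard care.
- Intervention at 3 months against control at 6 months: computable, but it mixes the arm effect with 3 months of elapsed time. No unexposed control score at 3 months and no intervention score at 6 months exists to separate them.

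**Which contrasts remain under the text?**

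- 3 months (both accounts): before crossover and therefore clean, but Follow-up data collection provides no contact with controls at that time and Table 2 leaves the control cell blank.
- 6 months (Secondary outcome measures only): would serve, but the K10 subsection and {18a} omit it, and Table 2 leaves the intervention cell blank.
- 12 months (both accounts): controls have had 12 − 6 = 6 months of the program. This compares earlier with later start, not program with usual care.

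No account that the protocol gives consistently yields a same-time comparison with unexposed controls.

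**Related mismatch.** Table 2 also leaves the control 3-month cell blank for illness control, unplanned visits and PIH, while Secondary outcome measures and {18a} include 3 months.

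**The case against.** The strongest reply is that the comparison is impossible only if Table 2 overrides the text. Read literally, the text gives both arms a 3-month score before crossover, and {20a} foresees longitudinal models. The scales are secondary, with no stated power.

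Much of this stands. The defect is first an internal contradiction, and the statement that no same-time comparison exists is conditional on Table 2. A longitudinal model could be fitted, but before crossover it would rest on an assumed time course that the data cannot test. The text is also not a free way out, because its 3-month control score conflicts with the rule on contact as well as with the table.

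A reader might infer three stronger things that the documents do not support.

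- *That the second hypothesis cannot be tested at all.* This holds only for a same-time comparison on these scales if Table 2 governs.
- *That the primary sustained response is judged on 3, 6 and 12 months in one arm and 6, 9 and 12 in the other.* No section says which visits decide it, and illness control is marked in both arms at 6 and 12 months.
- *That 3-month control data on markers and unplanned visits are lost.* These come from the electronic medical record and can be extracted without contact. The blank cells are a schedule mismatch.

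Self-efficacy is a named secondary outcome, yet no listed instrument is presented as measuring it. That is a separate point and carries no weight here.

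**Conclusion.** The point holds in conditional form. If Table 2 is followed, PedsQL, TMQ and K10 have no post-baseline visit common to both arms, so the corresponding parts of the second hypothesis have no same-time comparison between randomized groups. Three sections of text contradict the table, and they also disagree with each other about 6 months. None of them, taken with the contact rule and the 6-month crossover, secures a comparison with unexposed controls.

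The size is three secondary scales. The primary outcome, unplanned visits and PIH are not shown to be affected beyond the blank 3-month control cells. The conclusion assumes that the table's marks are as printed and that no undescribed contact collects control questionnaires at 3 months.

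**What to change.** - In Table 2, add PedsQL, TMQ and K10 for the intervention arm at 6 months. The booster session and the PIH scale are already scheduled then, and controls already have questionnaires.
- Require the control 6-month set to be completed before the first program session, since Table 2 marks both at that visit.
- Name 6 months as the between-arm time point for these questionnaire outcomes only. The primary outcome keeps its 12-month definition.
- Align Secondary outcome measures, the K10 subsection and section {18a} with the amended table.
- Minor: extract control markers and unplanned visits at 3 months from the medical record, correct the PIH timing in the text or the table, and state that sustained response is judged on visits common to both arms.

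The alternative of collecting control questionnaires at 3 months, as the text implies, would also work, but it means changing the contact rule for controls.

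Cost: one extra set of 23 + 18 + 10 = 51 items for about 30 participants (60 recruited, 1:1) at an existing contact, one extra record extraction, and an amendment submitted to the ethics committee and the registry. Recruitment began in December 2021, so intervention participants already past 6 months when the change takes effect may lack this score, and their number should be reported.
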